**Autoimmune disease**

**Immunodeficiency**

**Active syphilis infection.** *Not excluded:* syphilis fully treated over six months ago.

**Asthma** other than mild, well controlled asthma. Exclude a participant who:

- Generally uses a bronchodilator (short acting beta2 agonist) daily, or
- In the past year, has (any of the following):
  - Had >1 exacerbation of symptoms treated with oral steroids (Note: oral steroid use is exclusionary within 168 days before first vaccination)
  - Used moderate to high dose inhaled corticosteroids (e.g., more than the equivalent of 250 mcg fluticasone; 400 mcg budesonide; 500 mcg beclomethasone; or 1000 mcg triamcinolone/flunisolide, as a daily dose) or theophylline
  - Needed emergent care, urgent care, hospitalization, or intubation for asthma

**Diabetes mellitus** type I or type II, including cases controlled with diet alone. *Not excluded:* history of isolated gestational diabetes.

**Thyroid disease or thyroidectomy** requiring medication during the last 12 months.

**Angioedema within the last 3 years** if episodes are considered serious or have required medication within the last 2 years

**Hypertension**

- If a person has been diagnosed with hypertension during screening or previously, exclude for hypertension that is not well controlled. Well controlled hypertension is defined as blood pressure consistently  $\leq 140$  mm Hg systolic and  $\leq 90$  mm Hg diastolic, with or without medication, with only isolated, brief instances of higher readings, which must be  $\leq 150$  mm Hg systolic and  $\leq 100$  mm Hg diastolic. For these participants, blood pressure must be  $\leq 140$  mm Hg systolic and  $\leq 90$  mm Hg diastolic at enrollment.
- If a person has not been diagnosed with hypertension during screening or previously, exclude for systolic blood pressure  $\geq 150$  mm Hg or diastolic blood pressure  $\geq 100$  mm Hg at enrollment.

**BMI**  $\geq 40$ ; or, BMI  $\geq 35$  with more than 1 of the following: age  $> 45$ , systolic blood pressure  $> 140$  mm Hg, diastolic blood pressure  $> 90$  mm Hg, smoking, known hyperlipidemia. A person with BMI over 35 should be asked about other contributory health risks.

**Bleeding disorder** diagnosed by a doctor (e.g., factor deficiency, coagulopathy, or platelet disorder requiring special precautions)

**Malignancy** *Not excluded: a participant with a surgical excision and subsequent observation period that in the investigator's estimation has a reasonable assurance of sustained cure and/or is unlikely to recur during the period of the study.*

**Seizure disorder** *Not excluded: a participant with a history of seizures who has not required medications or had a seizure for 3 years.*

**Asplenia:** any condition resulting in the absence of a functional spleen

**Psychiatric condition** that precludes compliance with the protocol. Specifically excluded are persons with any of the following:

- Psychoses within the past 3 years
- Ongoing risk for suicide
- History of suicide attempt or gesture within the past 3 years

*Additional exclusion criteria for female participants: pregnancy, or breast feeding, or planned to become pregnant during the period of study participation.*

## 7 Safety and immunogenicity evaluations

### 7.1 HIV counseling and testing

- Participants will be counseled at all scheduled visits during the trial on avoidance of HIV infection.
- Participants will be counseled about potential negative impacts of testing positive due to the vaccine.
- Participants will be counseled on the risks of seeking HIV testing outside of the network during study participation, and discouraged from doing so.

#### 7.1.1 Distinguishing intercurrent HIV infection from vaccine-induced positive serology

The study product is known to elicit an antibody response to HIV proteins. Therefore, vaccine-induced positive serology is likely to occur in this study. Several precautionary measures will be taken to distinguish intercurrent HIV infection from vaccine-induced positive serology:

- Participants will have clinical evaluations at visits specified in Appendix C.
  - Signs or symptoms of an acute HIV infection syndrome, an intercurrent illness consistent with HIV-1 infection, or probable HIV exposure would prompt a diagnostic work-up per the HVTN algorithm for Recent Exposure/Acute Infection Testing to determine HIV infection.
  - Diagnostic HIV-1 EIAs will be performed from blood draws at multiple time points throughout the trial (see Appendix B). If positive test results are observed post-vaccination, the Laboratory Program or approved diagnostic laboratory will proceed with the HVTN algorithm to distinguish vaccine-induced antibody responses from actual HIV infection.
- Continued follow-up will identify subsequent HIV infections or address concerns in participants whose HIV-1 EIA is positive at the end of the study. All participants who have positive or indeterminate HIV-1 serology at the last study visit (as measured by the standard anti-HIV antibody screening tests) will be offered post-study HIV-1 diagnostic testing (HIV-1 EIA, Western blot, PCR) periodically and free of charge as medically/socially indicated (approximately every 6 months). This follow-up will be available until the EIA/Western blot pattern no longer yields positive or indeterminate results due to vaccine or until HIV infection is confirmed.
- Potential participants identified as being HIV infected during screening and participants who become HIV infected during the study will be referred for medical treatment and management of the HIV infection. These individuals will also be referred to appropriate ongoing clinical trials or observational studies.

### 7.2 Immunogenicity evaluation

The ability of the vaccine to induce humoral responses and/or epitope-specific CD8+ and CD4+ T-cell responses will be evaluated by the methods described below.

## **7.2.1 Humoral immunogenicity studies at HVTN**

### **7.2.1.1 Binding antibodies by ELISA**

Binding antibodies to commercially available Env will be assessed by the HVTN Laboratory Program by ELISA using single serum dilutions (1/50 or 1/100) on samples from all study participants. Any of the time points that yield positive results, defined as an OD of  $\geq 0.2$ , in the initial ELISA may be subject to endpoint titration ELISA employing 6 (2-7-fold) serial dilutions of serum beginning at a 1/50 or 1/100.

### **7.2.1.2 Neutralizing antibody assay**

If binding antibody titers meet the criteria established by the Protocol Team for examining neutralizing antibodies and if other prime-boost regimens using these vaccines (e.g., HVTN 052 and 057) show neutralizing antibody activity, then HIV-1 specific neutralizing Ab assays will be performed on serum samples from study participants displaying high ELISA titers. The assays will test neutralization of HIV-1 MN and the HIV-1 strain represented in the vaccine constructs.

## **7.2.2 Cellular immunogenicity studies at HVTN and the NIAID Vaccine Immune and T-Cell Antibody Laboratory (NVITAL)**

Both the HVTN and VRC will evaluate cellular immunogenicity. The data from NVITAL will contribute to the data package that the VRC will use to determine whether the products and alternate routes of administration qualify for further evaluation. The data from the HVTN laboratory will be used for independent analysis, to evaluate how these vaccines compare to other vaccines, and in determining the HVTN's involvement in additional trials with these products.

### **7.2.2.1 IFN-gamma ELISpot**

Ex vivo T-cell responses will be assessed by IFN- $\gamma$  ELISpot using cryopreserved PBMC stimulated overnight with synthetic peptide pools that correspond to the proteins encoded by the vaccine constructs. ELISpot assays will be performed with specimens collected at baseline and at visits indicated in Appendix B. Responses will be reported as number of spot forming cells (SFC) per  $10^6$  cells/well recognizing any specific peptide pool.

### **7.2.2.2 Flow cytometry**

Flow cytometry will be used to examine HIV-specific CD4+ and CD8+ T-cell responses using ICS following stimulation with synthetic HIV peptides that correspond to the proteins encoded by the vaccine construct. ICS assays will be performed with specimens collected at baseline and at visits indicated in Appendix B. Responses will be reported as percentages of CD4+ or CD8+ T-cells recognizing any specific peptide pool. Additional cell surface markers or functional markers may also be analyzed.

## **7.3 Genotyping**

Molecular human leukocyte antigen (HLA) typing may be performed on enrolled participants using cryopreserved PBMC collected at baseline, initially in participants who demonstrate vaccine-induced T-cell responses at post-vaccination time points. Other participants (including placebo recipients) may be HLA-typed to support future studies of immunological interest at the discretion of the protocol chair and the HVTN Laboratory Program.

Other genetic markers, such as genes associated with immune responses or HIV-1 infection, may be performed on stored specimens.

#### **7.4 Ancillary studies**

Cryopreserved samples may be used to perform additional humoral and cellular assays to support standardization and validation of these assays, and to evaluate additional immunological assays of interest. These assays may include, but are not limited to, fine epitope mapping by flow cytometry or ELISpot, or flow cytometric tetramer analysis.

#### **7.5 Future use of stored specimens**

The HVTN may store blood from participants for future testing and research related to furthering the understanding of HIV or vaccines to the extent authorized in each study site's informed consent form, or as otherwise authorized under applicable law.

## 8 Statistical considerations

### 8.1 Overview

This study is a multicenter, open label, randomized trial. The data analysis will evaluate safety and immunogenicity of candidate vaccines with the boost administered intramuscularly (IM), intradermally (ID), or subcutaneously (SC) in the study groups.

### 8.2 Objectives

The primary objectives concern safety and immunogenicity of the study vaccines with the boost administered IM, ID, or SC. The secondary objectives concern secondary immunogenicity and social impact. See Section 5 for details.

### 8.3 Endpoints

#### 8.3.1 Safety

Assessment of product safety will include clinical observation and monitoring of hematological and chemical parameters. Safety will be evaluated by monitoring participants for local and systemic adverse reactions after each injection and for 12 months after the first injection.

The following parameters will be assessed:

- Local reactogenicity signs and symptoms
- Systemic reactogenicity signs and symptoms
- Laboratory measures of safety
- Adverse events

#### 8.3.2 Immunogenicity

Primary immunogenicity endpoints are:

- The magnitude of HIV-specific T-cell responses assessed by the magnitude of IFN- $\gamma$  ELISpot responses 4 weeks after the booster adenoviral vaccination.

Secondary immunogenicity endpoints are:

- The titer of HIV-specific binding antibodies assessed by ELISA.

Exploratory endpoints may include:

- The expression of HIV-specific T-cell surface and functional markers 4 weeks after the booster adenoviral vaccination assessed by flow cytometry.
- The titer of HIV-specific neutralization antibody assessed by neutralizing antibody assay.

Section 7 provides details of the immunogenicity assays that will be performed.

### 8.3.3 Social impacts

Social impact variables include any negative experiences or problems the participant experienced due to his/her participation in this study. The following social impacts will be followed during the course of the study: social, travel, work, school, health care, insurance, housing, military, and any additional impacts identified by a participant.

## 8.4 Accrual and sample size

Recruitment will target 90 healthy, HIV-uninfected adult participants. This study will consist of 3 groups. All groups will be enrolled in parallel and randomized to receive DNA prime administered via IM injection using Biojector® and adenoviral vector boost administered via IM, ID, or SC injection using needle and syringe. See the study Schema for details.

Since enrollment is concurrent with receiving the first study vaccination, all participants will provide some safety data. Hence, sample size calculations for safety in Section 8.4.1 are based on the target sample sizes. However, this is not true of the immunogenicity data. Therefore the sample size calculations in Section 8.4.2 account for 10% of enrolled participants having missing data for the primary immunogenicity endpoints, an estimate based on previous HVTN and AIDS Vaccine Evaluation Group (AVEG) studies.

### 8.4.1 Sample size calculations for safety

The goal of the safety evaluation for this study is to identify safety concerns associated with administration. Sample size calculations for safety are expressed in terms of the ability to detect rare events.

The ability of the study to identify rare events can be expressed by the maximum true rate of events that would be unlikely to be observed and the minimum true rate of events that would very likely be observed. Specifically, for each vaccine arm of the study ( $n=30$ ), there is a 90% chance of observing at least 1 event if the true rate of such an event is at least 8%; and there is a 90% chance of observing no events if the true rate is no more than 0.35%.

Probabilities of observing 0 or 2 or more events among arms of size 30 are presented in Table 8-1 for a range of possible true event rates. These calculations provide a more complete picture of the sensitivity of this study design to identify potential safety problems with the vaccine. In previous AVEG HIV vaccine trials, 3.5% of control participants experienced a serious adverse event; in HVTN vaccine trials (as of January 2006), about 1% of control participants had experienced such an event.

**Table 8-1 Probability of response for different safety scenarios**

| True event rate (%) | Pr(0/30) | Pr(2+/30) |
|---------------------|----------|-----------|
| 1                   | 0.740    | 0.036     |
| 3.5                 | 0.343    | 0.283     |
| 5                   | 0.215    | 0.446     |
| 10                  | 0.042    | 0.816     |
| 20                  | 0.001    | 0.989     |
| 30                  | <0.001   | >0.999    |
| 40                  | <0.001   | >0.999    |

An alternative way to describe the statistical properties of the study design is in terms of the 95% confidence interval about the event rate that would be obtained from the observed safety data. Table 8-2 shows the exact 2-sided 95% confidence intervals for the probability of an event based on a particular observed proportion. If none of the 90 participants receiving a vaccine regimen experience a safety event, the 95% exact 2-sided upper confidence bound for the rate of such events in the total vaccinated population is 4%. Restricted to any of the individual vaccine arms (n=30), the exact 2-sided upper confidence bound for this rate is 12%.

**Table 8-2 Exact 2-sided 95% confidence intervals based on observing a particular proportion of safety endpoints for arms of size n1 and n2**

| Observed proportion | Confidence interval (%) |
|---------------------|-------------------------|
| 0/30                | [0.0,11.6]              |
| 1/30                | [0.1,17.2]              |
| 2/30                | [0.8,22.1]              |
| 0/overall 90        | [0.0,4.0]               |
| 1/overall 90        | [0.0,6.0]               |
| 2/overall 90        | [0.3,7.8]               |

#### 8.4.2 Sample size calculations for immunogenicity

The main goal of this trial regarding immunogenicity is to determine if ID or SC route of administration of the Ad5 boost is superior to IM administration in eliciting vaccine-induced HIV-specific T cell responses. Because IM administration is easier to administer, IM administration would continue to be used with this product unless there is a large improvement in immune response. The immunogenicity outcomes involve both preliminary estimation and a formal comparison of the mean magnitude of T-cell responses among study groups. Since the standard error of the estimated mean response magnitude depends on the true population variance, several parameters for the sample size calculations for immunogenicity will be estimated from existing ELISpot assay data.

It has been observed from previous HVTN studies that the magnitude of T-cell responses assessed by the IFN- $\gamma$  ELISpot assay appears to be normally distributed after a logarithm transformation. Since logarithm transformations are more intuitive for interpreting fold differences, log-10 transformation will be adopted in the estimation of distribution parameters of the true underlying population distribution.

Consider the sample standard deviation to be 0.35 after log-10 transformation. Two-sided confidence intervals for the mean magnitude of the T-cell responses based on observing a particular mean magnitude of responses can be found in Table 8-3 for groups of size 30 and 27, accounting for 10% missing immunogenicity data.

**Table 8-3 Two-sided confidence intervals for the T-cell response based on observing a particular mean response magnitude in the vaccinees (n=30,27)**

| Observed mean magnitude* | 95% CI (n=30) | 95% CI (n=27) |
|--------------------------|---------------|---------------|
| 100                      | [75,134]      | [74,136]      |
| 150                      | [113,201]     | [111,204]     |
| 200                      | [150,267]     | [148,272]     |
| 250                      | [188,334]     | [185,339]     |
| 300                      | [225,401]     | [222,407]     |
| 350                      | [263,467]     | [259,475]     |
| 400                      | [300,534]     | [296,543]     |
| 450                      | [338,601]     | [333,610]     |
| 500                      | [375,668]     | [369,678]     |

\*Observed SFU per ELISpot well ( $\sim 2 \times 10^5$  PBMC). Response rates conventionally reported per  $10^6$  PBMC.

A formal comparison of the immunogenicity between the study groups (n=30) will also be performed. For example, a 2-fold difference in mean response magnitudes between two groups of size 30 is detectable with 82% power for a two-sided two-sample t-test with a Type I error rate of 0.05. Based on groups size of 30 and a sample standard deviation of 0.35 after log-10 transformation, additional power calculations for comparison of mean response magnitudes between arms that can be distinguished with statistical power of 80% and 90% are provided in Table 8-4. This calculation accounts for 10% of enrolled participants having missing data for the primary immunogenicity endpoints. Note that the sizes of differences that the trial is powered to detect are fairly large.

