**Table 8-4 Minimum detectable differences in mean response magnitudes between two arms (of size 30)**

| True mean response* Arm 1 | Minimum detectable mean response* Arm 2 |           |
|---------------------------|-----------------------------------------|-----------|
|                           | 80% power                               | 90% power |
| 100                       | 191                                     | 209       |
| 200                       | 382                                     | 418       |
| 300                       | 572                                     | 627       |
| 400                       | 763                                     | 836       |
| 500                       | 953                                     | 1045      |

\*Observed SFU per ELISpot well ( $\sim 2 \times 10^5$  PBMC). Response rate conventionally reported per  $10^6$  PBMC.

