#### **8.5.4 Immunogenicity analysis**

For the statistical analysis of immunogenicity endpoints, all data from enrolled participants will be used according to the initial randomization assignment regardless of how many injections they received. The only exception will be to exclude data from HIV-infected

participants at or post infection. Thus, for HIV-infected participants, only immunogenicity data from samples drawn prior to HIV infection will be included in the analysis.

If assay data are qualitative (i.e., positive or negative), then analyses will be performed by tabulating the frequency of positive response for each assay by arm at each time point that an assessment is performed. Binomial response rates will be presented with their corresponding exact 95% confidence interval estimates.

To compare the response rates of any two vaccine arms, a significant difference will be declared if the 2-sided 95% confidence interval for the difference in response rates between the two arms excludes 0. If assays are run at multiple time points, the probability of observing at least one positive response by a given time point and the probability of observing more than one response by a given time point will be estimated, with corresponding confidence intervals, for each vaccine arm using maximum likelihood based methods [53]. Missing responses will be assumed to be missing at random (i.e., conditional on the observed data the missingness is independent of the unobserved responses).

For continuous assay variables, overall differences between arms at a specific time point will be tested by a 2-sample t-test if the data appear to be normally distributed after certain power or logarithm transformations, or by utilizing the nonparametric Wilcoxon rank sum test if the transformed data are not normally distributed. More sophisticated analyses employing repeated measures methodology (for example, repeated measures ANOVA or generalized estimating equations) may be utilized to incorporate immune responses over several time points. However, inference from such analyses would be limited by the small sample size of this study. All statistical tests will be 2-sided and will be considered statistically significant if  $p \leq 0.05$ . Graphical descriptions of the longitudinal immune responses will also be given.

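### The 82% power for a 2-fold difference does not follow from its stated inputs, which give 87% to 91%, and it conflicts with Table 8-4

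*Protocol*

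**What the plan says.** Section 8.4.2 of the Protocol gives the only power figures for the primary immunogenicity objective, which compares ID with IM and SC with IM on ELISpot magnitude four weeks after the boost. The worked example is that "a 2-fold difference in mean response magnitudes between two groups of size 30 is detectable with 82% power". The same sentence names the test behind this figure: a t-test for two samples, two-sided, at alpha 0.05.

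Table 8-4 is introduced with the inputs "Based on groups size of 30 and a sample standard deviation of 0.35 after log-10 transformation". The text then adds: "This calculation accounts for 10% of enrolled participants having missing data for the primary immunogenicity endpoints". The table's title gives arms of size 30. Against an Arm 1 mean of 100 it lists 191 for 80% power and 209 for 90% power; against 500 it lists 953 and 1045.

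Section 8.5.4 uses the same alpha: "All statistical tests will be 2-sided and will be considered statistically significant if" p is at most 0.05. Section 8.5 waives multiplicity adjustment for safety and secondary immunogenicity endpoints. It states no division of alpha over the two primary route comparisons.

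**The concern.** All the inputs to the 82% are given: effect, standard deviation, test, alpha and arm size. The figure can therefore be checked, and it looked too low for a 2-fold difference of 0.301 log10 with a standard deviation of 0.35 and 30 per arm. Table 8-4 also lists a 2.09-fold difference at 90% power, which sits poorly with 82% at 2-fold in the sentence above it. The arm size is unclear too, because the text and title name 30 while 10% loss is said to be included, which would leave 27.

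At stake is whether a reader can rely on the stated sensitivity of the trial for a primary objective, and whether 90 participants are enough.

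**Working it through.** **Inputs (Section 8.4.2).** Difference d = log10(2) = 0.30103. Standard deviation s = 0.35 on the log10 scale. Two-sided alpha 0.05, two-sample t-test. Arm size n = 30, or 27 evaluable (30 × 0.9).

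**Check on the standard deviation.** Table 8-3 reproduces in all 18 cells from mean × 10^(±1.96 × 0.35/√n), rounded up. For example, with n = 27 and mean 100 it gives [74, 136]. So 0.35 is the value used in that section.

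**Power at 2-fold.** SE = s√(2/n), noncentrality = d/SE, and power = P(T > t_crit) for noncentral T with 2n − 2 degrees of freedom.

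- n = 30: SE = 0.35 × √(2/30) = 0.0904; noncentrality = 0.30103/0.0904 = 3.33; t_crit (58 df) = 2.002; power **90.6%** (normal approximation 91.5%).
- n = 27: SE = 0.35 × √(2/27) = 0.0953; noncentrality = 0.30103/0.0953 = 3.16; t_crit (52 df) = 2.007; power **87.3%** (normal approximation 88.5%).

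The stated 82% is reproduced by neither arm size. The gap is about 5 to 9 points, more than rounding or the choice of approximation explains.

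**Table 8-4 against the 82%.** All ten cells equal the Arm 1 mean times 10^0.28 (80% column) or 10^0.32 (90% column), rounded up: 100 × 1.9055 = 190.5, shown as 191; 500 × 2.0893 = 1044.6, shown as 1045. A 2-fold difference lies (0.3010 − 0.28)/(0.32 − 0.28) = 0.526 of the way between the columns. On the normal-quantile scale this is 0.842 + 0.526 × (1.282 − 0.842) = 1.073, or **about 86%**. The table therefore contradicts the 82%.

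**Table 8-4 against its inputs.** Detectable Arm 2 means against Arm 1 = 100, exact t, with the log10 difference in brackets:

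| Setting | 80% power | 90% power |
|---|---|---|
| Table 8-4 | 191 (0.28) | 209 (0.32) |
| alpha 0.05, n = 30 | 181 (0.257) | 199 (0.298) |
| alpha 0.05, n = 27 | 187 (0.272) | 206 (0.315) |
| alpha 0.025, n = 27 | 200 (0.301) | 221 (0.344) |

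No row matches. The nearest setting with the stated alpha is n = 27, where 0.272 and 0.315 become 0.28 and 0.32 if rounded up to two decimals. A normal approximation at alpha 0.025 with n = 30 gives 0.279 and 0.318 (190 and 208), which round to the same two values. The coarse rounding means that the table cannot identify which setting was used.

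**Where could 82% come from?** Alpha 0.025 with n = 27 gives 82.1% by normal approximation and 80.0% by exact t. Alpha 0.0167 with n = 30 gives 82.6% and 80.4%. Alpha 0.05 with n = 30 and a standard deviation of 0.40 gives 81.8% (t). The protocol states none of these settings.

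**The case against.** The strongest defence is that the error harms nobody. At the documented alpha the trial has more power than it claims. With 27 per arm the table's detectable ratios are only about 2% too large (1.91 against 1.87; 2.09 against 2.06), and the text itself warns that the detectable differences are fairly large. Endpoint, test and enrolment are untouched. This stands, and it limits the severity. It does not rescue the 82%, which is wrong on its own inputs and is contradicted by the table beside it.

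A reader might infer more: that both figures were computed at alpha 0.025, as a split over the two route comparisons, and that the table leaves out the 10% loss. The documents do not support this. Both sections that state an alpha for these tests give 0.05, and no split is mentioned. The 82% can be approached by several routes. Table 8-4 is compatible with alpha 0.05 and 27 per arm once its rounding is taken into account, so neither the unstated alpha nor the omitted loss is established.

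A reader might also object that Table 8-3 uses normal rather than t quantiles. That table illustrates precision at an assumed standard deviation, and with n = 27 the change would be from [74, 136] to [73, 138]. It needs no correction.

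**Conclusion.** The 82% is wrong as written. On the stated inputs the power at 2-fold is 90.6% with 30 per arm and 87.3% with 27 evaluable. It also disagrees with Table 8-4, which implies about 86%, and the table does not give the exact values at alpha 0.05 for either arm size. The cause is unknown.

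At the stated alpha the error is conservative, so it gives no ground for saying that the trial is too small. This rests on the protocol's own standard deviation of 0.35, equal variances, approximate normality on the log10 scale, and alpha 0.05 for each comparison. The point should be fixed because these are the only power figures for a primary objective. It is not a flaw in the design.

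**What to change.** In Section 8.4.2, base the power sentence and Table 8-4 on 27 evaluable per arm (30 enrolled, 10% missing) and the stated two-sided alpha of 0.05. Restate the power for a 2-fold difference as 87%. Put the evaluable size in the title of Table 8-4 and replace its rows (80% / 90% power) as follows:

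| Arm 1 | 80% | 90% |
|---|---|---|
| 100 | 187 | 206 |
| 200 | 374 | 413 |
| 300 | 561 | 619 |
| 400 | 748 | 825 |
| 500 | 935 | 1032 |

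Only if the sponsor confirms that alpha was meant to be split over the two primary route comparisons, state 0.025 per comparison in both Section 8.4.2 and Section 8.5. In that case use 80% power at 2-fold and 200 / 221 against 100, with the other rows in proportion.

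The cost is one sentence and one table, plus a line in Section 8.5 if a split is confirmed. Enrolment does not change. At alpha 0.05 the corrected figures are more favourable than those now printed.
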